### Primary outcome

The main objective is to evaluate the benefit of the WEBAPPAC web-application on patient adherence to adjuvant hormone therapy for breast cancer 18 months after treatment start.

The primary endpoint of the study is the proportion of patients with adherence failure of hormone therapy within 18 months after treatment start, in each arm. Adherence failure of hormone therapy will be defined by at least one of the following items:

Adherence score less than 6 on the 8-item Morisky questionnaire (MMSA8) [22–25], completed at 18 months;Treatment discontinuation since at least one month, documented in the patient’s adherence notebook;Absence of hormone therapy dispensation for at least one month, documented on the hormone therapy prescription, with traceability of each dispensation noted on the prescription;Permanent discontinuation of hormone therapy as declared by the patient at the 18-month follow-up medical consultation.

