### Study assessments

The overview of study assessments and procedures is detailed in Table 2.

**Table 2 Tab2:** Overview of study assessments in the WEBAPPAC study

TIME Point	Before inclusion	Inclusion and randomisation ^a^	Day 15^b^	6 Week^b^	3-months^b^	6-months^a^	18-months ^a^
		Visit 1				Visit 2	Visit 3
Informed consent	•	•^a^					
**Training of the patient in the Web application**		**•** ^**b**^					
**Medical examination** (medical history, weight, height, vital parameters)		**•** ^**a**^					
**Quality of life self-report questionnaires (EORTC QLQ C30; and QLQ BR23)**		**•** ^**a**^				**•** ^**a**^	**•** ^**a**^
**Anxiety and Depression Questionnaire (HADS)**		**•** ^**a**^				**•** ^**a**^	**•** ^**a**^
**Assessment of pain using the Visual Analogue Scale (VAS)**				**•** ^**b**^	**•** ^**b**^	**•** ^**a**^	**•** ^**a**^
**Pain score (BPI)**		**•** ^**a**^					**•** ^**a**^
**Morisky Medication Adherence Scale (MMAS8)**				**•** ^**b**^	**•** ^**b**^	**•** ^**a**^	**•** ^**a**^
**Measurement of user experience (self-questionnaire (SUS))**							**•** ^**b**^
**Phone call** to ensure that there are no technical difficulties.			**•** ^**b**^				
**Evaluation of adherence to hormone therapy treatment by traceability of delivery, adherence notebook and patient declaration**						**•** ^**a**^	**•** ^**a**^
**Return to work and/or daily activities**					**•** ^**b**^	**•** ^**a**^	**•** ^**a**^
**Number of calls to the breast nurse**						**•** ^**a**^	**•** ^**a**^
**Patient satisfaction with 18-month follow-up**							**•** ^**a**^

^a^ During consultation at the Center with the medical oncologist in both arms

^b^ Only for the experimental arm (WEBAPPAC), at home

At inclusion, patients will be asked to complete the following self-questionnaires: EORTC QLQ-C30 and BR23, HADS, and BPI.

During their participation, assessments will be realized 6 and 18 months after the initiation of hormone therapy as follows:

Adherence to hormone therapy (MMAS8, adherence notebook, dispensation, patient report).Quality of life (QLQ-C30 and BR23 self-questionnaires).Anxiety and depression level (HADS self-questionnaire).Return to work and/or daily activities.Pain level (VAS at 6 and 18 months, and BPI at 18 months only).Patient follow-up satisfaction (VAS, at 18 months only).

In addition, patients in the experimental arm will be asked to fulfill the following assessments:

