### Statistical design overview

#### Sample size determination

In literature, discontinuation of adjuvant hormone therapy is reported in 20% of cases. The option of offering patients a web-application rather than an accompaniment by a standard follow-up would appear relevant if it allows to observe a difference in discontinuation rate of at least 10%. According to a two proportion z-test, with a two-sided alpha risk of 5% and a power of 80%, 398 patients (199 per arm) are required to observe a significant difference in the discontinuation rate of at least 10%, assuming an adherence failure rate of 20% in the control arm. To take into account a 10% drop-out rate, we plan to enroll 438 patients overall (219 per arm).

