#### Statistical analyses

Exploratory analyses of the data will provide, for quantitative variables, the mean, standard deviation, median, quartiles, and number of missing values; for qualitative variables, we will calculate the frequencies and their 95% confidence intervals. The demographic and clinical characteristics of the patients will be described. An intent-to-treat analysis will be conducted. The statistical significance level is set at 5% for each statistical analysis and confidence interval.

The main objective is to compare the proportion of patients who had adherence failure 18 months after hormone therapy treatment start between the two groups. This comparison will be performed using a two-tailed Chi-squared test at the 5% level. All the measures will be used in order to reduce the number of patients lost to follow-up. For patients lost to follow-up at 18 months, with available data on adherence to hormone therapy at 6 months, data on adherence at 6 months will be retained, otherwise patients in the experimental arm will be considered as non-adherent and patients in the standard arm will be considered as adherent.

For secondary objectives, secondary endpoints will be described used the methods above described. The comparison of these endpoints between both groups will be performed using the Chi-squared test (or Fisher’s exact test if necessary) for qualitative variables, and through a Student’s test (or non-parametric Wilcoxon Mann Whitney test if necessary) for quantitative variables.

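### Carrying the 6-month adherence status forward treats patients who were adherent at month 6 and then lost as non-failures on an 18-month endpoint, with 12 months unobserved

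*Protocol article*

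**What the plan says.** The Primary outcome section defines the endpoint as "the proportion of patients with adherence failure of hormone therapy within 18 months after treatment start, in each arm". Any one of four items makes a failure. Two can first arise at any time in the window: a gap of a month or more in dispensing, and "Treatment discontinuation since at least one month, documented in the patient’s adherence notebook". The other two are tied to month 18: a Morisky score below 6 completed then, and "Permanent discontinuation of hormone therapy as declared by the patient at the 18-month follow-up medical consultation".

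The Statistical analyses section sets two rules for patients lost at 18 months. If 6-month adherence data exist, "data on adherence at 6 months will be retained", in both arms. If they do not, "otherwise patients in the experimental arm will be considered as non-adherent and patients in the standard arm will be considered as adherent".

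Under Study assessments, "assessments will be realized 6 and 18 months after the initiation of hormone therapy". Table 2 shows no assessment common to both arms between those two visits.

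**The concern.** The endpoint accumulates over 18 months, but for one group of patients it is read at month 6. Someone adherent at month 6 and then lost is given zero risk for the remaining 12 months. The article offers no reason to expect no failures in that period. Its Background points the other way, citing a study in which more than 30% had stopped their aromatase inhibitor two years after starting.

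Two things are at stake. If loss is equal in the arms, a true difference is diluted. If loss is unequal, the arm that loses more patients has more of its failures hidden and looks better. The arm-specific worst case, which is conservative against the app, does not help here because it covers only patients with no 6-month data.

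**Working it through.** **Inputs from the article.** Failure 20% in the control arm, 10-point difference (so 10% in the app arm), two-sided 5%, 80% power, 199 per arm, 219 per arm enrolled, 10% drop-out with no split by arm or by time.

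**The plan's own figure.** The pooled two-proportion formula without continuity correction, for 20% v 10%, gives 198.96, so 199 per arm. This matches. All randomised patients get an outcome under the stated rules, so the comparison has 219 per arm; without carry-forward bias, power there is 83.7%.

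**Inputs that must be assumed.** The 6-month failure rate, loss after month 6 in each arm, and the failure risk of lost patients.

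**1. Equal loss, constant hazard, lost patients at average risk.** The 6-month risk is 1 − (1 − p)^(6/18).
- Control: 1 − 0.80^(1/3) = 7.17%. App: 1 − 0.90^(1/3) = 3.45%.
- With 10% lost after month 6, control is 0.9 × 0.20 + 0.1 × 0.0717 = 18.7%.
- App is 0.9 × 0.10 + 0.1 × 0.0345 = 9.3%.
- The difference is 9.4 points instead of 10. Power at 219 per arm is about 81% (normal approximation).
- With no true effect, both arms fall by the same amount and there is no bias.

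**2. Unequal loss, no true effect, high-risk lost patients.** Take 20% true failure in both arms and 50% true 18-month risk in lost patients. Under a constant hazard those same patients have a 6-month risk of 1 − 0.5^(1/3) = 20.6%, and these failures are carried forward correctly. Each lost patient therefore hides 0.50 − 0.206 = 0.294 of a failure.

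| Loss after month 6 | Observed failure |
|---|---|
| 5% | 0.20 − 0.05 × 0.294 = 18.5% |
| 10% | 0.20 − 0.10 × 0.294 = 17.1% |
| 15% | 0.20 − 0.15 × 0.294 = 15.6% |

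Loss of 5% v 10% creates a spurious difference of about 1.5 points, and 5% v 15% about 2.9 points, in favour of the arm with more loss.

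**3. Unequal loss over a range.** Observed rate = p − L × r × p × (1 − g). L is the share lost after month 6, r the risk of lost patients relative to p (1 to 2), and g the share of 18-month failures already present at month 6 (one third to 0.7).
- *Control 15%, app 5%, true 20% v 10%.* Mild end (r = 1, g = 0.7): 0.20 − 0.15 × 0.20 × 0.3 = 19.1% v 0.10 − 0.05 × 0.10 × 0.3 = 9.85%, or 9.25 points, power 79%. Severe end (r = 2, g = 1/3): 0.20 − 0.15 × 2 × 0.20 × 2/3 = 16.0% v 0.10 − 0.05 × 2 × 0.10 × 2/3 = 9.33%, or 6.7 points, power about 55%.
- *Control 5%, app 15%, no true effect.* Mild end: 19.7% v 19.1%, or 0.6 points. Severe end: 18.7% v 16.0%, or 2.7 points. Both favour the app. The two-sided rejection rate is 5.3% to 11.4% instead of 5%.

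**The case against.** Several points on the other side are sound.

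- **The equal-loss effect is small.** At 10% loss under a constant hazard the power of about 81% is still above the planned 80%, and there is no bias under the null. This stands.
- **Understatement is not certain.** Month-6 failures are carried as failures. Because the Morisky item counts at month 18, a low 6-month score that later recovers would overstate failure. This stands. Understatement remains the more likely net direction, because discontinuation and dispensing gaps can only add up.
- **The direction is not fixed.** Only the app arm gets notifications and reminders (Experimental arm section), which makes more loss in the control arm plausible. That would mask a benefit. A reader might infer that the rule mainly threatens a false positive. That would need more loss in the app arm, which is possible but which the article gives no particular reason to expect.

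Three stronger readings are tempting and not supported.

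- A reader might set the 50% risk of lost patients against the 7.2% 6-month risk of an average patient and find about 2.1 points (5% v 10% loss) or 4.3 points (5% v 15%). That mixes two hazards; the consistent figures are 1.5 and 2.9.
- A reader might infer that the rule discards a failure already recorded between month 6 and loss. The endpoint makes any one item sufficient, and the rule does not say that such a record is overruled. The wording should be made explicit, but it is not shown to be wrong.
- A reader might infer that carry-forward will govern most lost patients. The timing of loss is nowhere given. The article also commits to limiting loss and, under Withdrawal from study, to following patients who withdraw early unless they refuse.

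Finally, imputation from observed data assumes that loss is ignorable given those data. It does not by itself remove bias from informative loss. This stands and shapes the fix.

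**Conclusion.** The point holds for patients adherent at month 6 and then lost. For them the primary-analysis rule answers a 6-month question where the endpoint asks an 18-month one. It is a stated rule for the primary comparison, not a detail left to an analysis plan.

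Its size cannot be read from the article. Equal loss of about 10% costs roughly half a point of a 10-point difference in the constant-hazard case. The material risk is unequal loss. A 10-point imbalance towards the control arm could reduce a true 10-point effect by between under one and more than three points. The same imbalance towards the app arm could create an advantage of up to about 3 points where none exists. These figures depend on the assumed loss by arm, the share of failures present by month 6, and the risk in lost patients. Since the direction depends on which arm loses more, the rule cannot be called conservative. The change should be made, but the finding does not show that the trial's result will be wrong.

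**What to change.** - State that any failure item documented before loss counts as a failure.
- For the other patients lost after month 6, multiply impute 18-month failure within arm, using 6-month adherence data, hormone-therapy type and baseline data. The 6-month data then inform the outcome without replacing it.
- Keep carry-forward as a sensitivity analysis.
- Add a sensitivity analysis for informative loss, for example a higher failure risk in lost patients than imputation gives, or the arm-specific worst case applied to all lost patients.

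The cost is a change of wording, modest extra programming and slightly wider intervals. No new data are needed. The change should be fixed before the analysis.

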### Study experimental plan

The study will be proposed by breast nurses or physician oncologists to patients who meet the eligibility criteria. An explanation of the study and an information note will be given to them. Patients will be enrolled in the study once provided their written informed consent. Then, the randomization will be performed on the eCRF portal, stratified on the type of hormone therapy (Aromatase Inhibitor (AI) or Tamoxifen), as these treatments differ in terms of patients’ age at prescription, tolerance profile and adherence difficulties.

Patients will be assigned, according to a 1:1 randomization, to one of the following arms:

Experimental arm: WEBAPPAC web-application support (WEBAPPAC arm).Control arm: standard support.

The patients will be recruited over 30 months. Their participation will last 18 months.

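### For patients lost without 6-month adherence data, the primary analysis imputes failure in the experimental arm and success in the control arm, removing 1.1 points of the planned 10-point effect per 1% so imputed

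*Protocol article*

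**What the plan says.** Protocol article, Statistical analyses: the main objective is a comparison of 18-month adherence failure between arms, on an intent-to-treat basis. "This comparison will be performed using a two-tailed Chi-squared test at the 5% level". The same paragraph gives a two-step rule for patients lost at 18 months.

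- Step 1, the same in both arms: where 6-month adherence data exist, they stand in for the 18-month result.
- Step 2, only where there are no 6-month data: "otherwise patients in the experimental arm will be considered as non-adherent and patients in the standard arm will be considered as adherent".

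The rule belongs to the main comparison. It is not labelled a sensitivity analysis, and no other missing-data rule is given for the primary endpoint.

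Protocol article, Sample size determination: "398 patients (199 per arm) are required", "assuming an adherence failure rate of 20% in the control arm" and a 10-point difference to detect. Drop-out is then allowed for: "To take into account a 10% drop-out rate, we plan to enroll 438 patients overall (219 per arm"). The section does not say what share of those drop-outs is expected to lack 6-month data.

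**The concern.** Step 2 replaces a missing outcome with a value that depends on the arm and on nothing observed. Every patient who reaches it moves the estimate against the application, whatever the reason for the loss, so no missing-data mechanism makes the rule neutral between the arms. Such a rule is useful as a worst-case bound, but here it produces the trial's main estimate and its main p-value.

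Two things are at stake. One is power: the sample size adds patients for drop-out but makes no allowance for a shrinking effect. The other is the meaning of a two-sided test: if the application does nothing, the rule alone can produce a significant result against it.

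**Working it through.** **Inputs (Protocol article).** From Sample size determination: control failure 20%, planned difference 10 points (so 10% in the experimental arm), two-sided alpha 5%, power 80%, 199 per arm evaluable, 219 per arm enrolled, 10% drop-out. From Study experimental plan: 1:1 allocation. From Statistical analyses: two-tailed chi-squared test.

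**The plan's own figure.** For two proportions with pooled null variance and mean rate 0.15:

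n per arm = [1.96 × √(2 × 0.15 × 0.85) + 0.8416 × √(0.20 × 0.80 + 0.10 × 0.90)]² / 0.10² = (0.9897 + 0.4208)² / 0.01 = 198.96, so 199 per arm and 398 in all. This matches the plan. Then 398 × 1.10 = 437.8, or 438, which also matches. With 219 per arm and no loss, power is 84%.

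**Effect of step 2.** Let m be the share of each arm that reaches step 2. Assume that m is equal in the two arms and that everyone else, including patients carried forward from 6 months, fails at the planned 20% or 10%.

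- Control failure: 0.20(1 − m)
- Experimental failure: 0.10(1 − m) + m
- Difference, control minus experimental: 0.10(1 − m) − m = 0.10 − 1.1m

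Each 1% so imputed therefore costs 1.1 points: 0.9 from the experimental arm and 0.2 from the control arm. The difference is zero at m = 0.10/1.1 = 9.1%.

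**Power for benefit at 219 per arm.** This is Φ[(d − 1.96 s₀)/s₁], where d is the difference, s₀ its pooled standard error and s₁ its unpooled standard error. For example, at m = 5%, d = 0.045, s₀ = 0.0357 and s₁ = 0.0356, so the power is Φ(−0.70) = 24%. As m is not given in the plan, it is shown as a range up to the full 10% drop-out.

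| m | Patients per arm | Control v experimental | Difference (points) | Power for benefit |
|---|---|---|---|---|
| 0% | 0 | 20.0% v 10.0% | 10.0 | 84% |
| 1% | about 2 | 19.8% v 10.9% | 8.9 | 74% |
| 2% | about 4 | 19.6% v 11.8% | 7.8 | 61% |
| 3% | about 7 | 19.4% v 12.7% | 6.7 | 48% |
| 5% | about 11 | 19.0% v 14.5% | 4.5 | 24% |
| 10% (extreme: no drop-out has 6-month data) | about 22 | 18.0% v 19.0% | −1.0 | about 1% |

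**No true effect (20% in both arms).** Control failure becomes 0.20(1 − m) and experimental failure 0.20(1 − m) + m, so the difference is −m. Each tail is nominally 2.5%.

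| m | Significant harm | Significant benefit |
|---|---|---|
| 2% | about 7.5% | about 0.7% |
| 5% | 25% | below 0.1% |
| 10% (extreme) | 70% | below 0.1% |

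**Comparison with a symmetric rule.** If the same patients count as failures in both arms, the rates are 0.20(1 − m) + m and 0.10(1 − m) + m, and the difference is 0.10(1 − m). Power is about 79% at 2%, 71% at 5% and 60% at 10%. Most of the damage in the first table therefore comes from the asymmetry and not from the loss itself.

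**The case against.** The rule is prespecified, open, and conservative for the claim the trial wants to make. The objective is to show benefit, and with no true effect the rule makes a false claim of benefit less likely, not more. That is correct. It does not answer the loss of power, nor the inflated chance of declaring harm under a two-tailed test.

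The affected group may also be small. Step 1 removes from it everyone with 6-month data. The 6-month consultation belongs to the standard care pathway in both arms. The article also commits to limiting losses and to following patients who stop early unless they wish otherwise. This stands, and it is why the size is given as a range. But 1% of each arm, about two patients, already puts power below the planned 80%.

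Three stronger readings are tempting and are not supported:

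- A reader might infer that every lost patient is imputed by arm. Step 1 rules this out.
- A reader might infer that the plan's 10% drop-out reverses the planned effect. That 10% is total drop-out. Reversal needs more than 9.1% of each arm, about 91% of the planned drop-outs, to lack 6-month data, and nothing in the article says so. Even if all of them did, the result would be 18% v 19%, practically no difference. At lower shares the effect is diluted, not reversed.
- A reader might infer that the sample size treats drop-outs as removed at random. The section says nothing about the mechanism. It supports only the narrower statement that adding patients does not allow for dilution.

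**Conclusion.** The concern holds for patients lost without 6-month data. The rule as written biases the primary estimate against the application by 1.1 points per 1% of patients so imputed. It takes power for benefit from 84% to 61% at 2% and to 24% at 5%, and it raises the chance of a spurious finding of harm from 2.5% to about 7.5% and 25% at the same shares. The 10% figures are an extreme case, not the plan's expectation.

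The sizes rest on equal loss in the two arms and on planned failure rates among all other patients. The direction of the bias needs neither assumption about the planned rates nor a particular reason for loss, because step 2 fixes the outcome by arm. This should be corrected before the analysis, since it concerns the only primary endpoint.

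**What to change.** Use one rule for both arms in the primary analysis for patients lost without 6-month data. The preferred choice is multiple imputation of 18-month failure within arm, from hormone-therapy type and baseline data, with results combined by Rubin's rules. Keep the present opposite-outcome rule only as a labelled worst-case sensitivity analysis.

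Multiple imputation assumes that loss is explained by the observed data, which is doubtful if patients disengage because they have stopped treatment. A second sensitivity analysis should therefore count these losses as failures in both arms. That alternative also dilutes the effect, though far less than the present rule, as the comparison above shows.

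The cost is a paragraph of protocol or analysis-plan wording and some programming, with no extra patients or visits. The primary analysis would no longer be the most conservative one available, but that bound would still be reported.

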### Data management

A Web Based Data Capture (WBDC) system will be used for data collection and query handling. The investigator will ensure that data are recorded on the eCRFs as specified in the study protocol and in accordance with the instructions provided.

The investigator ensures the accuracy, completeness, and timeliness of the data recorded and of the provision of answers to data queries according to the Clinical Study Agreement. The investigator will sign the completed eCRFs. A copy of the completed eCRFs will be archived at the study site.

### Withdrawal from study

The reasons for why a patient may discontinue to participate to the study include the following circumstances:

Patient’s decision (the data already collected during the search can be kept and exploited unless the patient opposes it).Need to initiate another anti-tumor treatment than hormone therapy.Patient lost to view.Investigator’s decision.

Any patient who prematurely withdraws from the study will continue to be followed, unless she wishes to withdraw from the study.

